## Abstract

**Introduction:**

The standard of care for patients with localised rectal cancer is radical surgery, often combined with preoperative neoadjuvant (chemo)radiotherapy. While oncologically effective, this treatment strategy is associated with operative mortality risks, significant morbidity and stoma formation. An alternative approach is chemoradiotherapy to try to achieve a sustained clinical complete response (cCR). This non-surgical management can be attractive, particularly for patients at high risk of surgical complications. Modern radiotherapy techniques allow increased treatment conformality, enabling increased radiation dose to the tumour while reducing dose to normal tissue. The objective of this trial is to assess if radiotherapy dose escalation increases the cCR rate, with acceptable toxicity, for treatment of patients with early rectal cancer unsuitable for radical surgery.

**Methods and analysis:**

APHRODITE (A Phase II trial of Higher RadiOtherapy Dose In The Eradication of early rectal cancer) is a multicentre, open-label randomised controlled phase II trial aiming to recruit 104 participants from 10 to 12 UK sites. Participants will be allocated with a 2:1 ratio of intervention:control. The intervention is escalated dose radiotherapy (62 Gy to primary tumour, 50.4 Gy to surrounding mesorectum in 28 fractions) using simultaneous integrated boost. The control arm will receive 50.4 Gy to the primary tumour and surrounding mesorectum. Both arms will use intensity-modulated radiotherapy and daily image guidance, combined with concurrent chemotherapy (capecitabine, 5-fluorouracil/leucovorin or omitted). The primary endpoint is the proportion of participants with cCR at 6 months after start of treatment. Secondary outcomes include early and late toxicities, time to stoma formation, overall survival and patient-reported outcomes (European Organisation for Research and Treatment of Cancer (EORTC) Quality of Life Questionnaires QLQ-C30 and QLQ-CR29, low anterior resection syndrome (LARS) questionnaire).

**Ethics and dissemination:**

The trial obtained ethical approval from North West Greater Manchester East Research Ethics Committee (reference number 19/NW/0565) and is funded by Yorkshire Cancer Research. The final trial results will be published in peer-reviewed journals and adhere to International Committee of Medical Journal Editors guidelines.

**Trial registration number:**

ISRCTN16158514.

Strengths and limitations of this studyA Phase II Trial of Higher Radiotherapy Dose in the Eradication of Early Rectal Cancer is a prospective, multicentre randomised controlled trial, in contrast to previous studies of organ preservation that have primarily been retrospective, single centre or single arm.The trial offers treatment for patients who are not good candidates for (standard) surgical management, thus serving a group of patients often excluded from clinical trials.Long-course radiotherapy may be intolerable for some very frail patients, for whom short-course treatment may be preferential; this study will not assess short-course radiotherapy.The phase II design is focused on generating preliminary evidence of efficacy; a subsequent phase III trial will be required to evaluate longer term clinical impact.The study has embedded a strong focus on patients and their assessment of outcomes, including patient-reported outcome measures and a translational substudy of patient treatment preferences.

## Introduction

Colorectal cancer is the third most common cancer in the UK. Each year, around 42 000 new cases are diagnosed, with over one-quarter within the rectum.^1^ The standard of care for patients with localised rectal cancer is radical surgery combined with a selective use of preoperative radiotherapy and adjuvant chemotherapy. Radical surgery consists of total mesorectal excision (TME) which is an oncologically effective treatment for early stage rectal cancer; only 2% and 12% of patients will experience local or distant failure, respectively.^2–5^ However, radical surgery is associated with risks of operative mortality, significant morbidity and the frequent need for stoma.

Mortality following elective major colorectal cancer surgery has fallen significantly in recent years and the 2020 UK National Bowel Cancer Audit Annual Report, relating to 2018–2019, shows overall 90-day mortality of 3%.^6^ However, postoperative mortality for rectal cancer increases with age as demonstrated in the Dutch TME trial^7 8^ and is highly dependent on patients’ general physical fitness, with significantly increased 30-day mortality in patients with American Society of Anesthesiologists grade III and above physical status.^9^

In the 2020 UK National Bowel Cancer Audit,^6^ 86% of patients with rectal cancer had a stoma following major resection, including 78% of patients undergoing anterior resection. Eighteen months later, 29% of these patients still had a stoma. Stoma-related morbidity affects at least 50% of patients; with the most common problems including high-output stomas, stoma prolapses, small bowel obstruction and wound infections.^10^ Among the patients not undergoing radical resection, many are older or frailer, with comorbidities, or those who may struggle to manage a stoma. Surgery is often not a good option for these patients yet there is no standard alternative treatment.

An alternative approach to surgery is the use of radiotherapy with or without chemotherapy (chemoradiotherapy, CRT) to try to achieve a sustained clinical complete response (cCR) and potential long-term tumour control. Registration studies of patients with (primarily) locally advanced cancer who have achieved a cCR after neoadjuvant treatment, and opted for non-surgical management, have reported on the oncological safety of this approach.^11–13^ A systematic review of 23 cohort studies of patients managed non-surgically following cCR suggested a pooled 2-year local regrowth rate of 21.3% in 575 cCR patients. The vast majority (93.2%) of patients with local regrowth were subsequently managed with salvage surgery.^14^ Consequently, a policy of ‘active surveillance’ is increasingly being adopted for patients in whom post-CRT endoscopy and MRI suggest a cCR.

Most published studies have focused on an ‘opportunistic’ approach in patients achieving a cCR following CRT as part of standard clinical management rather than exploring dedicated organ preservation strategies (planned intent). Only a small minority of locally advanced rectal cancers achieve a cCR with standard CRT; however, changing our focus to earlier cancer, which are more likely to respond to chemoradiotherapy, there is the potential for considerably improving response rates. This opens for studies of dedicated and upfront non-surgical management strategies using chemoradiotherapy as a definitive treatment.

There is moderate evidence of a radiation dose–response relationship for pathological tumour regression after preoperative (chemo)radiotherapy.^15 16^ Currently, there is no high-level evidence as to whether dose escalation increases the cCR rate, although selected publications have reported high cCR and organ preservation rates with high-dose chemoradiotherapy for early cancers.^17 18^ Early response and toxicity data for a single-arm phase II organ preservation study delivering 62 Gy (tumour) and 50.4 Gy (lymph nodes) have also been presented in abstract form.^19^ The non-randomised nature of these studies is a major limitation, particularly with the inclusion of small and early cancers which are more likely to respond.^20^ Additionally, there is limited evidence of the optimum dose level for dose escalation, though experience from anal cancer and preliminary data from two ongoing Danish studies (NCT02438839, NCT04095299) indicate that 62 Gy can be safely delivered to a confined target volume in 2.2 Gy per fraction.

Modern radiotherapy techniques, including intensity-modulated radiotherapy (IMRT) and volumetric arc therapy (VMAT) with image guidance (image-guided radiotherapy, IGRT), improve conformality of treated volumes. Theoretically, this will reduce early and late toxicities when compared with conventional 3D conformal planning.^21^ These advances offer the possibility of increasing the dose to the tumour without excessive morbidity of surrounding normal tissues. Dose escalation with simultaneous integrated boost can thus be achieved without significantly altering the dose delivered to the organs at risk, and without extending the overall treatment time.

To further minimise radiation-induced side effects, a risk-adapted target volume can be used. The risk of pelvic lymph node involvement or distal mesorectal nodal involvement is very low for patients with early rectal cancer.^22 23^ Additionally, local recurrences are unlikely to be found above the level of the S2/3 interspace.^24^ In early rectal cancer, it is thus doubtful that traditional, large elective treatment volumes are indicated. Therefore, it is reasonable to reduce the target volume to the peritumoral region of the primary tumour and the mesorectum.^25 26^

A Phase II trial of Higher RadiOtherapy Dose In The Eradication of early rectal cancer (APHRODITE) phase II study will use modern radiotherapy techniques to investigate the efficacy and safety of escalated dose radiotherapy for non-surgical treatment of early-stage rectal cancer in patients not suitable for standard surgical management.

## Methods and analysis

### Design and aim

APHRODITE is a phase II, multicentre, open-label randomised controlled trial of IMRT, with select use of concomitant chemotherapy, in patients with early-stage rectal cancer (T1-3bN0, maximum diameter ≤4 cm) who are deemed not suitable for radical TME surgery by their multidisciplinary team (MDT). The primary aim is to assess whether radiotherapy dose escalation increases the cCR rate at 6 months from the start of CRT, compared with standard radiotherapy dose CRT, with acceptable toxicity. Patients may receive full dose, reduced dose or no concomitant chemotherapy. A total of 104 eligible patients will be recruited from 10 to 12 UK radiotherapy sites. Participants will be randomised on a 2:1 basis to receive escalated dose or standard dose chemoradiation. The participant pathway can be seen schematically in figure 1. The study protocol and this manuscript have been written in accordance with the Standard Protocol Items: Recommendations for Interventional Trials guidelines.

**Figure 1 F1:**
[figure not shown]
Trial schema. *At treating team discretion, concurrent chemotherapy can be used either at 75% dose or omitted completely. This choice must be declared prior to randomisation. CTCAE, Common Terminology Criteria for Adverse Events; ECOG, Eastern Cooperative Oncology Group; EORTC, European Organisation for Research and Treatment of Cancer; IMRT, intensity-modulated radiotherapy; LARS, low anterior resection syndrome; TME, total mesorectal excision.

### Trial objectives

The primary objective of APHRODITE is to compare the proportion of participants with a cCR at 6 months from the start of CRT. A composite definition for cCR is used, including digital rectal examination (DRE), rectal endoscopy and pelvic MRI, defined by:

No evidence of either mucosal tumour or submucosal swelling on white light endoscopy. A flat white scar remains, with or without telangiectasia.No palpable tumour on DRE.High-resolution pelvic MRI scanning shows either a linear scar only or dense fibrosis with no obvious tumour signal (mrTRG 1 or 2).^27 28^

This definition of cCR follows international consensus.^29^ Every effort will be made to ensure trimodality assessment (endoscopy, DRE and MRI). If such is not possible, confirmation should always include a rectal endoscopy and one other (DRE, MRI). Detailed guidance on MRI and endoscopy is provided in separate trial guidelines. The protocol does not require use of biopsy for response evaluation.

Currently research is unclear whether high-dose radiotherapy increases the rate of superficial mucosal ulcerations in the presence of a complete primary tumour response. Therefore, an alternative definition of the primary endpoint, with the inclusion of superficial mucosal ulceration classified as cCR, will be explored in a sensitivity analysis.

The secondary objectives of APHRODITE evaluate the safety and tolerability of dose escalation based on:

Acute toxicities as per Common Terminology Criteria for Adverse Events (CTCAE V.5.0) (measured weekly during and up to 2 weeks after end of treatment).Treatment compliance (both radiotherapy and, if received, concomitant chemotherapy).Toxicities during follow-up as per CTCAE V.5.0 (measured up to the 24-month follow-up point).

The longer term activity of dose escalation will be evaluated based on:

Time to stoma formation (time from randomisation to stoma formation—colostomy or ileostomy).Overall survival (time from randomisation to death from any cause).Patient-reported outcome measures (PROMs), assessed by the European Organisation for Research and Treatment of Cancer (EORTC) Quality of Life Questionnaires QLQ-C30^30^ and QLQ-CR29,^31^ low anterior resection syndrome (LARS) questionnaire^32^ and additional EORTC QLQ items from the Item Library relevant for organ preservation.

### Study population

Eligible patients are those with early-stage rectal cancer who are deemed by their MDT not suitable for radical TME surgery because either:

The patient is thought to be at increased surgical risk due to specific medical comorbidity or general frailty.The patient has marked anxiety at the prospect of having a stoma.It is anticipated that the patient would have difficulty managing a stoma postoperatively, for example, due to physical problems.

See table 1 for a full list of inclusion and exclusion criteria.

**Table 1 T1:** Inclusion and exclusion criteria

Inclusion criteria	Exclusion criteria
1. Biopsy-confirmed adenocarcinoma of the rectum.	1. Nodal involvement on MRI (ie, N1–N2)* or discontinuous tumour deposits (N1c).
2. Age 18 years or over.	2. The presence of EMVI discontinuous with the primary tumour on MRI.
3. Able to provide written informed consent.	3. Involvement of anal intersphincteric plane or external anal sphincter or adjacent organs; or tumour involves/breaches levator ani.
4. Patient deemed unsuitable for TME surgical resection, see main text for details.	4. Tumour grown through and breached mesorectal fascia.
5. Patient suitable for pelvic radiotherapy or chemoradiation: ECOG PS 0–2.	5. Signet ring carcinoma or tumours histopathologically containing a neuroendocrine component; or dominant mucinous tumour on MRI.
6. Primary tumour staged T1–T3b*, and maximum tumour diameter ≤4 cm, both on MRI.	6. Undergone an attempt at complete local resection of their cancer.
7. No unequivocally involved lymph nodes, NX and N0 eligible*.	7. Definite distant metastases (equivocal distant metastases are permitted).
8. Tumour visible on MRI.	8. Defunctioning colostomy/ileostomy fashioned.
9. Superior aspect of tumour is at or below a horizontal line drawn from the anterior aspect of the S2/3 junction on pretreatment MRI.	9. Previous pelvic radiotherapy; or prior systemic chemotherapy for colorectal cancer.
10. For low rectal tumours, superior to the puborectalis sling, the mesorectal fascia or levator is: Clear (>1 mm from disease to levator ani or mesorectal fascia). Or threatened (≤1 mm from disease to levator ani or mesorectal fascia). Or mesorectal fascia is involved but not breached.	10. Prior invasive malignancy unless disease free for a minimum of 3 years (excluding basal cell carcinoma of the skin or other in situ carcinomas).
11. Blood counts fulfilling: Estimated creatinine clearance ≥50 mL/min. Absolute neutrophil count >1.5×10^9^/L; platelets >100×10^9^/L. Serum transaminase concentration <3× upper limit normal (ULN), bilirubin concentration <1.5× ULN.	11. Women who are pregnant, breast feeding or of childbearing potential and unwilling to use contraceptives.

*Tumour, node, metastases (TNM) staging as per UICC 8th Edition.

ECOG, Eastern Cooperative Oncology Group; EMVI, extramural venous invasion; PS, Performance Status; TME, total mesorectal excision; UICC, Union for International Cancer Control.

### Randomisation and recruitment

A computer-generated minimisation programme incorporating a random element will be used to allocate patients on a 2:1 basis to receive escalated dose or standard dose chemoradiation, ensuring arms are well balanced for the following factors:

Randomising site.T-stage (<T3 vs T3).Chemotherapy use (either 100% or 75% dose) versus no chemotherapy use.

Randomisation will be performed centrally via the University of Leeds Clinical Trials Research Unit (CTRU) automated 24-hour randomisation system. The registration and randomisation process will be instigated by on-site research staff; patient consent form must be attained prior to registration (see online supplemental file 1).

10.1136/bmjopen-2021-049119.supp1Supplementary data

Recruitment will take place over 2 years, with an estimated monthly recruitment rate of four to six patients per month. APHRODITE opened in February 2020, with expected recruitment completion by winter 2022. The study has and will be presented at national and international meetings, increasing clinical awareness. A trial website and dedicated Twitter account will be used to further increase exposure, highlighting the trial population criteria to treating clinicians and MDT members. Based on preliminary feedback from clinicians and patient representatives in the study design phase, the 2:1 allocation between the intervention and control arms will make recruitment attractive for patients with limited standard treatment options.

### Sample size

The target sample size is 104 participants (70 experimental: 34 control), based on a two-group χ^2^ test of equal proportions, with continuity correction. Assuming a control arm cCR rate of 35%,^33^ using a one-sided test at 20% significance, 104 participants (incorporating a 5% loss to follow-up) will provide 80% power to detect an absolute difference of 20% (to 55%) between arms. Data suggest potential differences as great as 25% (in favour of the experimental arm).^17 34^

An inflated type I error rate of 20% is used as the aim is to show preliminary evidence of activity.^35 36^ The direct comparison with the control avoids the risk of incorrect decision-making due to uncertain historical control data.^37^

### Treatment regimen

Intervention arm: the primary tumour will receive 62 Gy in 28 fractions, with 50.4 Gy delivered to the surrounding elective mesorectal volume, using a simultaneously integrated boost.

Control arm: the primary tumour and elective mesorectal volume will receive a uniform 50.4 Gy in 28 fractions (preoperation standard dose).

A reduced mesorectum-only elective volume will be used, as appropriate for early-stage disease at low risk of nodal failure. All treatments will be planned and delivered using IMRT or VMAT, with extensive radiotherapy guidelines, based on the STAR-TREC (*S*ave the rectum by watchful waiting or *T*rans*A*nal microsurgery following (chemo) *R*adiotherapy versus *T*otal mesorectal excision for early *RE*ctal *C*ancer) trial target definition and treatment planning.^25 26^ Daily image guidance with cone beam CT will be mandatory and promotes precise treatment delivery, essential as the mesorectum and tumour exhibit significant changes in day-to-day position.^7 24^ See figure 2 for an example treatment plan.

**Figure 2 F2:**
[figure not shown]
Example treatment plans for the control arm (top panel: uniform 50.4 Gy in 28 fractions to the primary tumour and elective mesorectal volume) and intervention arm (lower panel: 62 Gy in 28 fractions to the primary tumour, 50.4 Gy to the elective mesorectal volume) for a single patient.

Concurrent chemotherapy will be used during CRT, either as single-agent oral capecitabine (825 mg/m^2^) given two times per day from Monday to Friday on the days of radiotherapy throughout the course of radiotherapy, or alternatively as intravenous 5-fluorouracil/leucovorin delivered once per day (5FU 350 mg/m^2^ plus leucovorin) concurrent with fractions 1–5 and 20–25 of radiotherapy (weeks 1 and 5). If the treating clinician decides a patient is not fit to receive the full (100%) dose of chemotherapy, due to comorbidities, or general frailty, they have the options to treat at 75% dose, or omit chemotherapy (radiotherapy alone). The intended chemotherapy treatment option must be declared for each patient *prior* to randomisation.

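### The 5-FU/leucovorin schedule contradicts itself: the second block is six administrations by fraction number but five by week label

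*Protocol article*

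**What the plan says.** The part of the Treatment regimen section that follows Figure 2 offers two concurrent chemotherapy options.

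- **Capecitabine** is named first and is "given two times per day from Monday to Friday on the days of radiotherapy throughout the course of radiotherapy".
- **The alternative** is "intravenous 5-fluorouracil/leucovorin delivered once per day", with 5-FU at 350 mg/m², "concurrent with fractions 1–5 and 20–25 of radiotherapy (weeks 1 and 5".

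Both arms have the same number of fractions: in the intervention arm "the primary tumour will receive 62 Gy in 28 fractions", and in the control arm the tumour and mesorectal volume "will receive a uniform 50.4 Gy in 28 fractions". Clinicians may also choose a 75% chemotherapy dose or no chemotherapy, declared before randomisation.

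The Trial objectives section lists, among the safety and tolerability objectives, acute toxicity and "Treatment compliance (both radiotherapy and, if received, concomitant chemotherapy". No other part of the article restates the 5-FU/leucovorin schedule.

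**The concern.** The schedule is given twice in one sentence, once as fraction numbers and once as week labels, and the reader should be able to convert one into the other. For the first block that works. For the second it does not: the fraction range is one fraction longer than the week it is said to occupy.

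At stake is the number of chemotherapy administrations planned for a participant on this regimen. The eligible population includes people judged unsuitable for surgery because of comorbidity or frailty, so the planned exposure should be unambiguous. The number also bears on two things the trial will report: toxicity, and compliance with concurrent chemotherapy.

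**Working it through.** **Inputs, all from the Treatment regimen section**

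- 5-FU/leucovorin once per day, hence one administration per listed fraction.
- Blocks: fractions 1–5 and 20–25, labelled weeks 1 and 5.
- 28 fractions in each arm.
- Five radiotherapy days a week. The main support is the sentence's own pairing of fractions 1–5 with week 1. The Monday-to-Friday wording supports it indirectly, since it describes capecitabine on radiotherapy days.

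**Step 1: count the fractions** (last − first + 1)

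- First block: 5 − 1 + 1 = 5
- Second block: 25 − 20 + 1 = 6

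**Step 2: convert fraction to week.** For fraction f at five per week, week = floor((f − 1)/5) + 1.

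- Fractions 1 to 5: (f − 1)/5 runs from 0 to 0.8, so all are in week 1. The article's first label is reproduced.
- Fraction 20: floor(19/5) + 1 = 3 + 1 = week 4.
- Fractions 21 to 25: (f − 1)/5 runs from 4.0 to 4.8, so all are in week 5.
- Fraction 28: floor(27/5) + 1 = 5 + 1 = week 6, so week 5 is a full five-fraction week.

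The second label is not reproduced. Fractions 20–25 fall in weeks 4, 5, 5, 5, 5, 5.

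**Step 3: try other ways of counting weeks**

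| Convention | Fractions 1–5 | Fractions 20–25 |
|---|---|---|
| 7-day weeks from fraction 1, any start weekday | week 1 | weeks 4 and 5 |
| Calendar weeks, Monday start | week 1 | weeks 4 and 5 |
| Calendar weeks, Tuesday to Friday start | weeks 1 and 2 | weeks 5 and 6 |

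No row gives week 1 for the first block and week 5 alone for the second. None can, because six once-daily fractions do not fit into a five-fraction week.

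**Step 4: size**

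- By fraction number: 5 + 6 = 11 administrations.
- By week label: 5 + 5 = 10 administrations.
- Ratio: 11/10 = 1.10, that is 10% more on the fraction-number reading.
- For 5-FU at the stated full dose: 11 × 350 = 3850 mg/m² against 10 × 350 = 3500 mg/m², a difference of 350 mg/m². The ratio is the same at the 75% dose.

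**The case against.** The count itself is hard to contest. The case on the other side is about consequences, and most of it stands.

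- **Sites do not work from the article.** The Ethics and dissemination section says the trial follows protocol version 3.0, which is not shown. The mismatch may be a one-digit slip made in writing the article. A reader might infer that sites are giving different numbers of administrations. Nothing in the document shows that, so the safety consequence is conditional on the full protocol having the same wording.
- **No compliance denominator is defined here.** A reader might infer that the compliance endpoint is left undefined, or that a participant given 10 administrations would score differently on the two readings. The article specifies no percentage-of-administrations measure. The Statistical analysis section promises summaries of delayed, modified and stopped treatment, and the scoring is properly left to the analysis plan. What remains is narrower: any summary that compares delivered with planned 5-FU needs one planned number.
- **Scope is limited.** 5-FU/leucovorin is the alternative to capecitabine, and chemotherapy may be omitted altogether. The number of participants who will receive it is not given.
- **The main inference is untouched.** The wording is common to both arms. If sites did read it differently, randomising site is a minimisation factor and the primary model adjusts for it.

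None of this removes the contradiction. The article chose to state the schedule in its operative treatment section, in intact running text, and stated it inconsistently. That is different from detail left to a fuller document.

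**Conclusion.** The contradiction is real. For participants on 5-FU/leucovorin, the sentence supports 11 administrations by fraction number and 10 by week label, a 10% difference in planned drug. This rests on one administration per listed fraction and five fractions a week, both of which the article supports.

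The practical weight depends on a document that is not shown. If the full protocol has the same wording, sites could deliver different exposures, with consequences for safety and for the reported chemotherapy compliance and toxicity. If only the article has it, this is an error in the published regimen. In either case the sample size, the error rates and the definition of the primary endpoint do not change.

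**What to change.** Compare the fraction range and the week label with the approved full protocol. Correct whichever is wrong in every place it appears, including the article. If the full protocol has the same wording, send sites a clarification, and use the reconciled number of planned administrations wherever 5-FU compliance is summarised. Which of the two is correct is for the sponsor and the clinical team; this review takes no position on it.

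The cost is one check and a wording correction, plus a notice to sites if their protocol is affected. No analysis or design feature has to change.
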